### Study design

The trial was a parallel, 18-month, randomised, double-blind, placebo-controlled trial with repeated measures every 6 months, totalling 4 measurement points. Because the primary hypothesis related to change in a continual developmental process, multiple repeated measures enable determination of the rate of change on the measures, allowing assessment of an intervention effect on a trajectory, rather than effects at a specific time point. Decline of the cognitive abilities vulnerable to ageing effects begins by the early 30s so although participants were screened for cognitive impairment, all were expected to experience cognitive decline to some extent; for instance, meta-analyses of cross-sectional data suggest that processing speed declines, on average, by approximately 20% at age 40 and by 40-60% at age 80 [34]. In terms of supplementation duration, studies have detected significant cognitive changes due to *n*-3 PUFA supplementation after 3-4 months [35,36]. However, these studies focused on clinical populations; change in normal populations would not be expected to be as rapid, or of the same magnitude and the longer duration allowed for the multiple testing points required to best test the hypothesis and conferred greater power to detect an effect.

The trial was co-ordinated from CSIRO Food and Nutritional Sciences, Adelaide, Australia. The protocol was explained to participants and written informed consent was obtained prior to study commencement. All experimental procedures were approved by the Human Research Ethics Committee of CSIRO and in compliance with the Helsinki declaration. The study follows Good Clinical Research Practice. Participants were encouraged to inform the trial research officer of any adverse events; these were recorded by the officer. Adverse effects suspected as being related to supplement use were reported to the trial clinical doctor for follow-up. Participants attended the centre every 3 months; every 6 months, to undergo their assessments, and 3-months after each assessment to obtain additional capsules and be followed-up. At these visits, adverse events were recorded, along with any changes in medication, supplement use, or general health.

### Participant recruitment

#### Sampling and criteria

Participants were recruited from metropolitan Adelaide, South Australia and surrounding areas via agencies and organisations for older citizens, public advertisements, and media releases. Information sheets explaining the study and asking for volunteers, were circulated in response to expressions of interest. To be eligible for inclusion, participants were required to be 65-90 years of age at screening, fluent in English, and agree to not commence their own *n*-3 fish-oil (or algal) supplementation throughout the duration of the study. Participants were excluded from study entry if they were taking *n*-3 fish-oil (or algal) supplements, had experienced any condition where cognitive impairment may be a consequence (e.g., head injury, other brain trauma, transient ischemic attacks, stroke, coronary artery bypass surgery, open heart surgery, degenerative neurological disease, history of alcohol/drug abuse), were taking doses of medications known to interfere with cognition, had a significant medical condition, were diagnosed with an intellectual disability, current major clinical depression, diabetes, dementia, or received a score less than 22/27 on a telephone-administered version [37] of the Mini-mental State Examination (MMSE) (equivalent to < 24/30 on the standard MMSE, the traditional cut-off for possible dementia).

#### Screening and information sessions

Individuals who expressed interest in participating were sent a questionnaire to obtain demographic information, history of health events, and specific questions to determine eligibility. Participants deemed eligible, based on the questionnaire responses, were contacted by a trained research officer and, if consenting, were administered a version of the MMSE via telephone - this method of administration has been validated for the MMSE [37]. Participants scoring less than 22 correct out of a potential 27 points were excluded. Subsequently, approximately two to three months prior to baseline testing, participants attended an information session, during which the study protocol and requirements were explained to them, queries were answered, and practice trials and examples of the cognitive tasks were given. Participants were asked to maintain their usual diet over the course of the study. After written consent to participate was obtained, individual administration of the standard MMSE was undertaken, to corroborate the telephone screening and to serve as an outcome measure.

#### Randomisation, allocation, and blinding

Participants were given a unique study number on entry into the trial. An independent researcher prepared allocation to treatment. Age-stratified, permuted-block randomisation, with mixed block-sizes ranging from two to eight (size unknown to study investigators until unblinding), with 1:1 allocation was employed. Participants were placed into 5-year age strata, and randomisation for each stratum followed a computer generated randomisation schedule. The researchers, project staff, and participants remained blinded to treatment allocation until the trial was completed and the database locked. Capsule bottles were labelled with participants' unique study numbers by an external company. Active and placebo capsules (opaque brown, oblong, and softgel; Blackmores Pty Ltd, Australia) and containers were visually identical, the fish-oil was the low-odour type, and 1% fish-oil was added to the placebo oil to help maintain blinding in the event of, for example, accidental piercing of the capsules or an aftertaste. At the study-end, participants were asked to guess which study arm they were in, to assess adequacy of blinding.

### Dietary intervention

#### Dietary intervention schedule

The intervention was administered for 18 months, starting immediately after baseline assessment, after which participants received their first 3-month supply of capsule bottles. For the study duration, participants returned to the CSIRO clinic every 3 months, received their next 3-month supply of capsules, and returned all unused capsules. The trial research officers recorded any reported side-effects of the capsules.

#### Compliance

Compliance was monitored via a count of all unused supplements returned at three-monthly intervals, along with self-report calendars, mailed back on a monthly basis throughout the trial. If participants' compliance fell below 85% on the basis of their calendars, they were contacted by a research officer who noted the reasons. Compliance also will be assessed by examination of erythrocyte membrane *n-*3 LC PUFA status and changes in status, via a blood sample taken at every 6 month-assessment.

#### *n*-3 LC PUFA capsule

The supplement was chosen to be DHA-rich on the basis that evidence suggests DHA is more related to cognition in ageing, than is EPA. The dosage for the current trial followed that of the first reported *n*-3 LC PUFA placebo-controlled intervention study focusing on cognitive decline in the elderly (albeit in AD patients [25]) that found a positive effect; hence, the study dose was 1720 mg DHA and 600 mg EPA daily. Each capsule contained 430 mg DHA and 150 mg EPA (EPAX 1050 TG/N *n*-3 concentrate, EPAX, Norway); participants were instructed to have a total of four capsules a day, two in the morning and two in the evening. The total *n*-3 LC PUFAs in the daily supplement were equivalent to approximately 150 g of salmon. There are no known risks associated with *n*-3 LC PUFA consumption at this level. Evidence supports the effectiveness of *n*-3 fish-oil supplements as providers of *n*-3 LC PUFAs, with *n*-3 LC PUFAs from fish-oil supplements being incorporated into erythrocyte membranes to a similar extent as *n*-3 LC PUFAs from dietary fish intake [38].

#### Placebo capsule

The placebo arm received capsules, each containing 990 mg of olive oil (Oil Seed Products, New Zealand) and 10 mg of fish oil (equivalent to 1.8 mg EPA and 1.2 mg DHA; omega-3 18/12, Ocean Nutrition, Canada) and consumed a total of 4 capsules a day. Unlike other oils, olive oil is not rich in *n*-3 or *n*-6 fatty acids and should thus have minimal effect on the *n*-6:*n*-3 ratio. Olive oil is high in mono-unsaturated fatty acids (MUFAs), which have in some epidemiological studies been associated with lower cognitive decline [39], yet it is thought that it is the polyphenolic content of the oil that might bear this effect. The amount of MUFAs in the capsules was very minor compared to the dietary consumption of MUFAs in those studies that found a cognitively protective effect (i.e., mean daily MUFA intake = 42.1 g [39]). The 4 g of low-polyphenol olive oil per day was thus considered non-problematic. The minimal amount of fish oil was added to help mask any difference between the placebo and active capsules and was not processed under nitrogen, rendering it less potent than that used in the active formulation.

### Assessment Administration

After the group information session, participants were scheduled one visit to the laboratory for assessment, every 6 months, for 18 months. Self-report questionnaires (see following section on study instruments) were mailed out to participants up to four weeks prior to each assessment visit, with instructions to complete and return them between one to two weeks prior to their assessment. Missing data or incorrectly completed questionnaires were thus identified beforehand and addressed during their assessment sessions. All physical measurements and cognitive testing were conducted at the same time in the morning at each session.

For each assessment visit, participants attended the clinic after an overnight fast, and a blood sample and physical measurements (height (at baseline only), weight, and blood pressure) were undertaken by trained phlebotomists and staff. Participants were then given a standardised breakfast in the centre, prior to undertaking the cognitive test battery. At baseline and final assessment, blood was taken for measurement of the following. Carotenoids, folate, and vitamin B12, were assessed, all having been associated with cognitive functioning in the elderly; this enables examination of cross-sectional associations between these measures and outcomes, and if necessary in the intervention analyses, to control for any potential differences between groups at baseline or any changes in these measures that differ between groups (despite randomisation). Glucose, glycated haemoglobin (HbA1c), lipid concentrations (total cholesterol, high-density lipoprotein (HDL), low-density lipoprotein (LDL), and triglycerides), and homocysteine were also measured at baseline and final assessment, because of associations between abnormalities in these parameters of metabolism and cognitive dysfunction [30]. Inclusion of these measures allows us to control for possible baseline differences between groups and potentially assess whether any changes on these measures due to the intervention mediate changes on the main outcome variables. Finally, our blood-derived measures included a high sensitivity assay for C-reactive protein (CRP), an inflammatory marker, plasma malondialdehyde (MDA), a marker of oxidative stress, and telomere length, a marker of oxidative stress and DNA damage. Oxidative stress and inflammation have been associated with cognitive decline or impairment [40,41] and are two postulated mechanisms through which *n*-3 LC PUFAs may exert an effect on cognitive functioning [34,35]; thus, we will examine cross-sectional associations between these measures and our cognitive outcomes, be able to control for potential differences between groups at baseline, and assess whether any changes due to fish oil supplementation mediate any change on the primary outcomes. Apolipoprotein E (ApoE) genotyping was also conducted in order to examine any differential effect of treatment due to carriage of the ApoE-ε4 allele. Blood was taken at the second and third assessment points in order to assess erythrocyte membrane fatty acid composition at each time point. *n*-3 LC PUFA status will be used to assess compliance/uptake post-hoc and we will also assess whether changes in *n*-3 LC PUFA status are associated with any changes on our outcomes. EPA levels in erythrocytes reflect intake over the past month or two, change linearly with dosage (up to 9 g/day), and increase is evident after 3 days of supplementation; EPA and DHA are incorporated equally effectively [42]. Dietary data for current *n*-3 and *n*-6 fatty acid intake was gathered at all time-points, to assess stability of dietary LC PUFA intake over the trial, a food frequency questionnaire (FFQ) was administered as a measure of typical nutrient intake over the preceding one-year period at baseline and at Time 4, and historical seafood consumption was also assessed. Cross-sectional associations between these measures and outcomes will be investigated, and if there are differences between groups at baseline or changes in *n*-3 or overall dietary intake which differ significantly between the active and control groups, then we will control for any potential effects of this on outcomes. Table 1 summarises the data collected at each time point.

**Table 1 T1:** Summary of measures assessed over the study duration.

Outcome measures and covariates	Time points (months)				
	
	~ -3	0	6	12	18
MMSE	x	x			x

Cognitive measures		x	x	x	x

Physical activity, functional capacity, and well-being measures		x	x	x	x

Height		x			

Blood pressure, weight		x	x	x	x

Erythrocyte membrane *n*-3 and *n*-6 fatty acid status		x	x	x	x

Serum folate and Vitamin B12, and plasma carotenoid levels		x			x

Lipids, glucose, glycated haemoglobin, homocysteine		x			x

Medications, supplement use, adverse events and health changes		x	x	x	x

ApoE genotype		x			

Inflammation (CRP), oxidative stress (MDA), and telomere length		x			x

Dietary data - general FFQ		x			x

Dietary data - *n*-3 consumption FFQ		x	x	x	x

Dietary data - historical seafood consumption FFQ			x		

Abbreviations: MMSE = Mini-mental state examination; *n*-3 = omega-3; *n*-6 = omega-6; FFQ = food frequency questionnaire; ApoE = Apolipoprotein E.

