#### Secondary outcome measures

Change in: MMSE; perceived health status, depressive symptoms, positive and negative affect, life satisfaction, self-reported cognitive functioning, and functional capacity, as assessed by the questionnaires below; blood pressure; biomarkers of glucose, glycated haemoglobin, triglycerides, total cholesterol, HDL, LDL, homocysteine, CRP, MDA, and telomere length.

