### Physical activity, functional capacity, and well-being

To assess changes in functional capacity and well-being, and potentially control for any effect of changes in mood or physical activity on cognitive functioning, validated questionnaires assessing everyday functioning (The Late Life Function and Disability Instrument [47,48]), depression (Centre for Epidemiology Studies Depression Scale [49]), self-reported cognitive functioning (Cognitive Failures Questionnaire [50], Prospective and Retrospective Memory Questionnaire [51]), subjective well-being (mood: Positive and Negative Affect Scale-Extended [52]; life satisfaction: Diener's Satisfaction with Life Scale [53], the Personal Wellbeing Index [54]), health-related quality of life (SF-36 [55], the sleep scale from the Nottingham Health Profile [56]), and physical activity (The Yale Physical Activity Survey [57]) were compiled as a general health and wellbeing questionnaire, which participants completed for each assessment. See Appendix 2 for descriptions of the questionnaires and derived scores.

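### Outcomes are to be controlled for on-trial changes, firmly for diet and conditionally for other measures, which can bias the randomised comparison

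*Protocol article*

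**What the plan says.** The protocol article deals with on-trial changes in three ways.

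- **Diet (Assessment Administration).** The commitment is firm. It applies to baseline differences. It also applies to on-trial changes in n-3 consumption and, in the article's words, "overall dietary intake which differ significantly between the active and control groups, then we will control for any potential effects of this on outcomes".
- **Carotenoids, folate and vitamin B12 (Assessment Administration).** The commitment is conditional. Where needed, the intervention analyses may use these measures "to control for any potential differences between groups at baseline or any changes in these measures that differ between groups (despite randomisation".
- **Mood and physical activity (Physical activity, functional capacity, and well-being).** The commitment is optional. One stated purpose of the questionnaires is to "potentially control for any effect of changes in mood or physical activity on cognitive functioning". No between-arm trigger is given.

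The remaining blood markers are handled differently. For glucose, HbA1c, lipids and homocysteine, control is foreseen for baseline differences only, and the on-trial data serve to "potentially assess whether any changes on these measures due to the intervention mediate changes on the main outcome variables". For CRP, MDA and telomere length the plan is likewise to control for baseline differences and to "assess whether any changes due to fish oil supplementation mediate any change on the primary outcomes".

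The Secondary outcome measures section lists "depressive symptoms, positive and negative affect, life satisfaction" among the outcomes of the intervention. The Analysis section defines the main test as the significance of the mean of the treatment slope added in the treated group's latent growth curve. It names no covariates.

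**The concern.** Randomisation balances what exists before treatment starts. It does not balance what treatment can alter afterwards. The text treats a between-arm difference in on-trial change like a baseline imbalance that randomisation failed to prevent and that the analysis should remove. In a double-blind trial, leaving aside differential loss to follow-up, such a difference is either chance or an effect of assignment. A rule triggered by that difference therefore tends to pick out the covariates most likely to lie downstream of the supplement.

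The estimate of the effect of assignment to fish oil is at stake. If the supplement changes the covariate and the covariate affects cognition, adjustment removes that part of the effect. If the covariate and cognitive change share unmeasured causes, such as developing illness, adjustment can create a spurious arm difference in either direction.

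**Working it through.** **1. The provisions side by side.** Timing is from Table 1.

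| Measure | Commitment to control for on-trial change | Between-arm trigger | Measured (months) |
|---|---|---|---|
| n-3 intake; overall diet | Firm | Yes, significant difference | n-3 questionnaire 0, 6, 12, 18; general questionnaire 0, 18 |
| Carotenoids, folate, B12 | Only where needed | Yes, changes that differ between groups | 0, 18 |
| Mood, physical activity | Optional | None stated | 0, 6, 12, 18 |
| Glucose, HbA1c, lipids, homocysteine | None; mediation analysis | – | 0, 18 |
| CRP, MDA, telomere length | None; mediation analysis | – | 0, 18 |

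The first three rows are at issue. In each, the change is observed after treatment begins, and for the vitamins and carotenoids it runs to the end of treatment. The last two rows show that the plan itself recognises such changes as possible consequences of the supplement. Mood adds a further conflict: depressive symptoms and affect are secondary outcomes and also possible covariates.

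**2. What adjustment does.** There is no stated figure to reproduce, so a simple linear model stands in for the growth curve. T is assignment, M the on-trial change in the covariate and Y the outcome, with unit residual variances:

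- M = a·T + u
- Y = τ·T + b·M + e, with correlation g between u and e (the shared cause)

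The effect of assignment, which the unadjusted comparison estimates, is τ + a·b. Adjusting for M gives E(Y | T, M) = τ·T + b·M + g·(M − a·T), so the coefficient of T becomes τ − a·g. The difference is −a·(b + g). It vanishes when a = 0, that is, when treatment does not move the covariate. Otherwise its sign depends on a, b and g.

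**3. Illustrations.** The document gives no value for a, b or g, so all values are assumptions. Each scenario was also simulated 4,000 times with 175 per arm (the plan's total of 350), adjusting only when M differed between arms at p < 0.05.

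- **Full mediation** (a = 0.4, b = 0.5, τ = 0, g = 0). True effect 0.4 × 0.5 = 0.20; adjusted 0. The trigger fired in 96% of trials. The mean estimate under the rule was 0.00, and rejection fell from 38% unadjusted to 5%.
- **Part mediation** (a = 0.3, b = 0.3, τ = 0.11, g = 0). True effect 0.11 + 0.09 = 0.20; adjusted 0.11. The mean under the rule was 0.12, and rejection fell from 43% to 20%.
- **No effect, shared cause** (a = 0.4, b = 0, τ = 0, g = 0.3). True effect 0; adjusted −0.4 × 0.3 = −0.12. The mean under the rule was −0.12, and false positives rose from 4.8% to 20%.
- **The same with a = 0.2.** Always adjusting gives −0.2 × 0.3 = −0.06. Under the rule, with the trigger firing in 46% of trials, the mean was −0.04 and false positives were 6.3%.
- **Chance imbalance only** (a = 0). No average bias under any analysis.

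The unadjusted comparison recovered the true effect in every scenario. These runs show direction and mechanism. They do not estimate what would happen in this trial.

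**4. Is the primary result protected?** The Analysis section names no covariates, but Assessment Administration expressly covers the intervention analyses and the outcomes. No section says which result is primary when the trigger is met, and none labels the adjusted model as sensitivity or explanatory.

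**The case against.** The strongest reply is that the main test is defined without covariates, and that the sentences at issue mainly explain why measures were collected. Whether a conditional adjustment replaces or accompanies the main test could be left to a full protocol or analysis plan. This stands in part: the article does not say that the adjusted model replaces the unadjusted one. But the diet sentence is a stated rule rather than a gap, and carrying it forward unchanged would carry the problem with it.

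A second reply is that bias needs the supplement to affect the covariate. Participants were asked to keep their usual diet, capsules were visually identical, and nothing in the article suggests that fish oil alters carotenoids, folate, B12 or overall diet. This is fair and limits the claim to what the rule can do. It does not rescue the rule: if the covariate is unaffected, adjustment is not needed to remove bias, and if it is affected, adjustment can cause bias.

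Three stronger readings are tempting and not supported:

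- A reader might infer that every blood marker, mood and activity is adjusted for whenever the arms differ. Only diet is firm, mood and activity have no such trigger, and the other blood markers go to mediation analysis, which is sound handling.
- A reader might infer that unblinded outcome results steer the choice. Staff stay blinded until the trial is completed and the database locked, and the trigger concerns covariates, not cognition.
- A reader might convert the planned power of .84 into a power loss. That power covers a difference in mean decline and/or in its variance, so it does not translate into a one-parameter test, and any mediated share would be invented.

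**Conclusion.** The concern holds in limited form. The article states a rule, firm for diet and conditional for carotenoids, folate and B12, to control intervention outcomes for on-trial changes that differ between arms. It also leaves open control for changes in mood or physical activity. Following these provisions can bias the estimated effect of assignment, in either direction, if the supplement affects the covariate. Chance imbalance alone gives no bias on average. Controlling for baseline variables is not part of this point. The rule is also inconsistent with the plan's own treatment of the other blood markers as possible mediators.

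The size of the bias cannot be derived from the document. The conclusion rests on the order of measurement and on the absence of any statement that keeps the unadjusted slope primary, not on the illustrative numbers.

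**What to change.** - State that the primary treatment-slope test is unadjusted, or adjusts only for baseline variables named in advance.
- Remove from the primary analysis the rule to control for on-trial changes in diet, carotenoids, folate or B12, and the option to control for changes in mood or physical activity.
- Report those changes by arm.
- Keep any model that contains them as a labelled exploratory mediation or sensitivity analysis that does not alter the primary conclusion, in line with the handling already foreseen for the other blood markers.

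The cost is wording only. No new data and no change in sample size are needed.
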